**Figure 2: The Stepped-Wedge Design**

[figure not shown]

A parallel design for this study was deemed unsuitable for both scientific and logistical reasons. Scientifically, because of the possibility, even likelihood, that in a parallel design the different groups of physiotherapists would be found to be unbalanced on some covariates, whereas the crossover designs have balance, reducing the influence of confounding variables because each physiotherapist subject serves as his or her own control (Brown et al., 2008). This is particularly important for this study as it could be argued that individual therapist attributes could have the greatest impact on patient outcomes. Logistically, the statistical efficiency of crossover designs requires fewer subjects than parallel designs; in a study requiring the use of available qualified clinical staff, and highly qualified clinical mentors, this would appear to be a valid consideration for design selection (Jones and Kenward, 2003). The stepped-wedge design was selected for four main reasons:

1. There is not a belief of equipoise – that is, it is rational to believe that the intervention is likely to result in good rather than harm for both the participating physiotherapists, who will receive Master’s level mentoring, and the clusters of patients “exposed” to the physiotherapists who have received training, making a parallel CRCT ethically less acceptable in that it would withhold the intervention from a larger proportion of physiotherapists and patients (Mdege et al, 2011; Brown & Lilford, 2006).
2. While a standard crossover CRCT would also satisfy this ethical concern, it would require the delivery of the intervention at the same time; this is logistically and practically difficult as the intervention (clinical reasoning facilitation via a mentoring programme) requires both specialist input (experienced MACP qualified mentors) and significant time input (150 hours of clinical mentoring), making the stepped-wedge design preferable as the intervention can be delivered in stages (Mdege et al, 2011; Hussey and Hughes, 2007; Brown and Lilford, 2006).

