### Settings and locations where the data will be collected

Patient outcome data will be collected at the first and last appointment of physiotherapy treatment at the six sites of outpatient musculoskeletal physiotherapy service delivery for the Cardiff and Vale University Health Board: The Barry Hospital, Cardiff Royal Infirmary, University Hospital Llandough, St. David's Hospital, University Hospital of Wales and Whitchurch Hospital. The 6 sites are organized into pairs for training purposes, and so to further reduce the risk of any potential contamination across sites, these pairs will form the 3 clusters which will be the unit of randomization as illustrated in figure 3. Long-term patient outcome data (12 months post-discharge) will be collected by participating physiotherapists by telephone contact.

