## Sample size

The primary outcome measure, the PSFS, shows that for any individual patient, the minimal detectable change (90%CI) for an aggregate of 3 or more activities is 2 points; the minimum detectable change (90%CI) for a single activity is 3 points. In this study, we are looking for a mean difference of 1 point greater improvement in PSFS scores of patients whose physiotherapists who have received the intervention compared with the PSFS scores of patients whose physiotherapists have not yet received the training, as well as a greater proportion of patients achieving the level of minimal detectable difference. The following data values were used for the power calculation: mean changes on the PSFS from usual training to the new training of 1 point, and a Standard Deviation within each group of 2. The standard deviation was on the basis of PSFS data collected from an audit of 191 patients who had received treatment at the University Health

Board physiotherapy department, which is a slightly more conservative estimate than standard deviation values of PSFS outcomes from published studies (Hefford et al., 2009, Young et al., 2010, Costa et al., 2009).

A paper published on the design and analysis of stepped wedge designs (Hussey and Hughes, 2007) investigated the statistical characteristics of the stepped wedge design for CRCTs, and through the use of theoretical calculations and simulation the authors outline a procedure for computing power in stepped wedge trials. Using this procedure, a power calculation was carried out by [name], Senior Lecturer in Statistics, Swansea University in discussion with the rest of the research team. The power calculation is summarised below:

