### **Power calculation: summary**

Following the notation of Hussey & Hughes (Hussey and Hughes, 2007), and defining

- I to be the number of physios (the maximum available would be 18; assuming recruitment of two-thirds of the maximum to be a realistic prospect, so we are primarily interested in  $I = 12$ )
- T to be the number of time points (4 time points are required to allow baseline measures and for 3 clusters to cross over from control to intervention, so we are primarily interested in  $T = 4$ )
- N to be the number of observations per physiotherapist per time point.

The model is

$$Y_{ijk} = \mu + \alpha_i + \beta_j + \theta X_{ij} + \varepsilon_{ijk}$$

where  $Y_{ijk}$  is the  $k^{th}$  observation at time  $j$  for physiotherapist  $i$ , and we assume that there is a random physiotherapist effect, so

$$\alpha_i \sim N(0, \tau^2)$$

and some random variation across observations, so

$$\varepsilon_{ijk} \sim N(0, \sigma_\varepsilon^2)$$

with independence everywhere. The  $X_{ij}$  are indicator variates, with value 0 before the intervention, and the value 1 thereafter. The range of indices are  $i = 1, \dots, I; j = 1, \dots, T$  and  $k = 1, \dots, N$ . We take  $\beta_T = 0$  in order to avoid identifiability problems, and wish to consider  $\vartheta$ , the difference in means in the control and intervention group. The variance of  $\hat{\vartheta}$  is given in equation (8) in Hussey & Hughes (Hussey and Hughes, 2007), and its calculation requires the specification of  $\sigma_\varepsilon^2$  and  $\tau^2$ , with  $N$  appearing through

$$\sigma^2 = \frac{\sigma_\varepsilon^2}{N}$$

Omitting some algebra, statistical power, based on the usual 95% confidence level, is defined by

$$1 + \Phi(-1.96 - \Delta) - \Phi(1.96 - \Delta)$$

where

$$\Delta = \frac{\theta_A}{\text{Var } \hat{\theta}}$$

and  $\Phi(\bullet)$  is the usual cumulative distribution function for the standard Normal distribution, and is implemented in EXCEL as =NORMSDISTO.

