#### Base case details

- Here, we take  $\theta = 1$  (that is, assume that the average effect of the intervention is 1), and (based on calculations on previous data) set  $\sigma_\varepsilon = 2$ . The remaining calculations are laid out in the attached spreadsheet, where, for illustration, if we take  $N = 9, \tau = 1$  then

$$Var(\hat{\theta}) = 0.12576 \dots,$$

and

$$\Delta = 2.819574$$

so that the power is

$$1 + \Phi(-1.96 - 2.8196) - \Phi(-1.96 - 2.8196) \simeq 1 - \Phi(0.8596) \simeq 0.805$$

- This implies that, in order to achieve a power of 0.8, we need a total of  $4 \times 12 \times 9 = 432$  observations.

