### **Statistical methods**

The analysis of stepped wedge trials has been clearly outlined in a published paper (Hussey and Hughes, 2007) and recommends processes for analysis of cluster-level means and individual level analysis in scenarios where cluster sizes are equal or unequal, and where variance is known or unknown. Processes for between cluster and within cluster analyses are outlined in order to avoid confounding the treatment effect with changes over time; these processes will form the basis for the statistical analysis for the study. If no temporal effects are found influencing the outcome, then a within-cluster analysis can be used to estimate the treatment effect. Statistical analysis will involve a classical ANOVA (so observations belong to one of two groups, each assumed to be independent of the others), supplemented by a random intercept which will reflect systematic differences across different clusters. Similar statistical methods have been used in other published stepped wedge trials (Schnelle et al., 1992, Bailey and Archer, 2004, Mdege et al., 2011).

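### The analysis places its only random intercept on 'clusters', a word used for staff for the 3 site pairs, while the sample size rests on a physiotherapist effect; the protocol should say which level is fitted

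*Protocol*

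**What the plan says.** The sample size (Power calculation: summary) is built on a stepped-wedge model in which the index i is the physiotherapist: "we assume that there is a random physiotherapist effect", with variance tau² and I = 12. The base case takes tau = 1, an intra-class correlation (ICC) of 0.2. The Other cases section and Appendix E carry the ICC up to 0.5.

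The Statistical methods section describes a classical two-group ANOVA with independent observations, "supplemented by a random intercept which will reflect systematic differences across different clusters". Step effects are to be included (Challenges in using this design).

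What 'cluster' means depends on the section:

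- Settings and locations: the six sites are paired and "these pairs will form the 3 clusters which will be the unit of randomization".
- Eligibility criteria for participant clusters: 12 physiotherapists in 3 clusters by site.
- Randomisation: clusters of physiotherapists, grouped by site, are allocated to the sequence.
- Table 5: Clusters 1 to 3, with four therapists each.
- Procedures (under the secondary outcomes): the patients of one therapist at one stage are also called a cluster.

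The reasons given for the design, under Figure 2, are that each physiotherapist acts as his or her own control, and that "it could be argued that individual therapist attributes could have the greatest impact on patient outcomes".

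**The concern.** The random intercept in the analysis and the one in the sample size appear to sit at different levels. If 'clusters' means site pairs, nothing in the fitted model represents the individual physiotherapist. Patients of one therapist are then treated as independent given the site pair, most of the therapist variance goes into the error term, and the own-control comparison used to justify the design is not made.

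Two analysts could follow the same sentence and fit different primary models, with different standard errors and p-values. The gap between the two models widens with the therapist variance, which the protocol itself regards as possibly the largest influence on outcome.

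**Working it through.** **Inputs, all from the protocol.** Effect theta = 1 and within-group SD 2, so σ² = 4 (Sample size). I = 12 physiotherapists, T = 4 steps, N = 9 patients per therapist per step, tau² = 1, two-sided 5% (Power calculation: summary; Base case details). Four therapists per site pair (Table 5). The ICC formula gives tau² = 2 at ICC 0.33 and tau² = 4 at ICC 0.5.

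**1. The protocol's own figure.** With s² = 4/9, U = 24, W = 224 and V = 56:

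Var = I·s²·(s² + T·tau²) / [(IU − W)·s² + (U² + ITU − TW − IV)·tau²] = (5.333 × 4.444) / (28.444 + 160) = 0.125786.

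1/√Var = 2.8196 and power = 0.805, as in Appendix E. The total is 4 × 12 × 9 = 432.

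**2. Where the therapist variance goes under a site-pair intercept.** The pair intercept absorbs only the average of four therapist effects, tau²/4. The rest stays as variation between therapists within pairs: 3 pairs × 3 degrees of freedom × 36 patients per therapist. The error degrees of freedom are 432 − 7 = 425 (3 pairs, 3 step contrasts, 1 intervention effect). Expected residual variance = 4 + (9 × 36 / 425)·tau² = 4 + 0.762·tau²:

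- tau² = 1: 4.76 (simulated 4.75)
- tau² = 2: 5.52
- tau² = 4: 7.05 (simulated about 7.0)

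**3. Precision with equal numbers.** The pair-level estimator has the same theoretical variance. With I = 3, s² = 4/36, pair variance 0.25, U = 6, W = 14, V = 14:

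Var = 3 × 0.1111 × (0.1111 + 1) / (4 × 0.1111 + 10 × 0.25) = 0.125786.

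So the loss comes mainly through the estimated standard error. At tau² = 4 the simulated mean standard error is 0.46, against a true SD of the estimate of 0.38.

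**4. Simulated operating characteristics.** Therapist effects generated, step effects fitted, REML, |z| > 1.96, 2,000 trials per setting. Each cell gives therapist intercept versus site-pair intercept.

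| ICC | Patients per therapist-step | Power | False positives |
|---|---|---|---|
| 0.2 | 9 | 80% vs 77% | 5.2% vs 6.5% |
| 0.33 | 9 | 80% vs 72% | 5.4% vs 3.3% |
| 0.5 | 9 | 79% vs 60% | 5.4% vs 2.5% |
| 0.2 | 3–15 | 79% vs 72% | 5.0% vs 8.2% |
| 0.33 | 3–15 | 78% vs 66% | 5.6% vs 8.9% |
| 0.5 | 3–15 | 77% vs 58% | 4.9% vs 9.6% |

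Repeat sets of 1,500 to 2,000 trials agree on the equal-number gaps: about 2 to 3 points at ICC 0.2, 7 to 8 at 0.33, and about 19 at 0.5. With the milder spread of 5–13 per cell, false positives under the site-pair intercept are 2 to 7%. If half the therapists are assumed to leave before the last one or two steps, they are 8.6% against 5.8% at ICC 0.2. The spreads and the departures are assumptions; the protocol gives no figure for either.

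**The case against.** The strongest reply is that the authors meant a therapist intercept. The Statistical methods section rests on a published stepped-wedge method, and the only place the protocol writes that model out makes the physiotherapist the index. Procedures also calls one therapist's patients a cluster. On that reading, sizing and analysis agree. This stands as a statement of possible intent, so a reader who infers that the protocol definitely drops the therapist level goes further than the text. It does not remove the ambiguity: every section that groups staff into clusters means site pairs, and none puts a physiotherapist term in the analysis.

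It can also be said that the level of a random effect belongs in a statistical analysis plan. That would hold had the protocol been silent. Here it names a level, and that level differs from the one it sized on.

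Three stronger readings are not supported:

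- **That the primary test will produce too many false positives.** The mention of unequal cluster sizes describes what the cited paper covers and does not predict recruitment. The plan is a fixed number per therapist and step, with sequential recruitment until the data set is complete. With equal numbers, the error rate is slightly above nominal at the base case and below it at higher ICC.
- **That all of tau² enters the residual.** About three quarters does.
- **That the base case is badly damaged.** With equal numbers, the power loss there is 2 to 3 points.

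**Conclusion.** The concern holds as a mismatch of level that the protocol leaves unresolved. Under the site-pair reading the analysis omits the physiotherapist effect used for sizing. With equal numbers this costs little at the base case and becomes serious in the upper part of the protocol's own ICC range, where power falls to about 60% against 79%. Inflation of false positives to 8 to 10% is conditional on strong imbalance, and there is little or none with 5–13 per cell.

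These sizes assume four therapists per pair, step effects in the model, a normal-theory Wald test and no additional site-pair variance. The point is separate from the small number of randomised units, which a therapist intercept does not cure.

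**What to change.** In Statistical methods, replace the cluster intercept with a physiotherapist random intercept and delete the wording that treats observations as independent. For the primary PSFS analysis on individual patient data:

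Y = step (fixed) + site pair (fixed) + theta·X + physiotherapist (random) + error.

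Site pair is fixed because three pairs are too few to estimate a variance.

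The cost is small. With equal numbers, fixed pair effects give Var = 3 × (4/36) × 4 / 10 = 0.1333 whatever tau² is, so 1/√Var = 2.739 and power is 0.782, against 0.805 as sized. Simulation puts the loss at 1 to 3 points at the base ICC. At that base case with equal numbers, the change therefore does not raise power above the site-pair intercept. Its benefit is a standard error that matches the design and power that holds at about 78% at ICC 0.5 instead of about 60%.

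Therapist ID is already a field on the patient outcome questionnaire, so no new data are needed. If a therapist intercept was always intended, this is a clarification of wording.

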### **Examples of use of this type of design**

A systematic review of stepped wedge trial designs in 2006 (Brown and Lilford, 2006) yielded 12 published trials and protocols evaluating a wide range of interventions, across different diseases in different settings. It was noted that the stepped wedge design was used most frequently in developing countries, particularly for evaluating interventions concerned with HIV. A subsequent systematic review (Mdege et al., 2011) included 25 studies, and concluded that the stepped wedge trial design has been mainly been utilised to evaluate interventions during routine implementation. In particular where interventions have been shown to be effective in more controlled research settings, or where evidence of effectiveness is lacking but there is a strong belief that they will do more good than harm. This latter scenario is closest to the rationale for this research project in that there is a strong belief that this intervention of clinical mentoring which is established both nationally and internationally by Master's programmes to develop physiotherapist expertise, should benefit patients who receive treatment from physiotherapists who have received such mentoring. Of particular interest from this last review are three studies which have used stepped wedge trials to evaluate educational interventions (Ni Mhurchu et al., 2010, Bailet et al., 2009, Howlin et al., 2007) underlining its usefulness for this research project.

There are also examples of the usage of this type of design in researching educational interventions with parallel crossover designs. From educating gait patterns in patients with Parkinson's disease (Nieuwboer et al., 2007) to the education of lay people in CPR techniques (Rawlins et al., 2009) and – most relevant to this research - to clinical skill education; crossover study designs are utilized to research educational interventions in developing technical surgical skills (Cho et al., 2008, Fikkers et al., 2004) and knowledge and clinical reasoning in both undergraduate and postgraduate clinicians (Bye et al., 2009, Cook et al., 2008, Lam et al., 2004, Murray et al., 1997a, Koles et al., 2005, Celebi et al., 2009, Cook et al., 2007, Cook et al., 2009, Cook et al., 2006). These are of interest for the justifications given for the selection of this methodological choice by the authors of studies in medical education: the ability to ensure that all participants receive all training (Bye et al., 2009, Celebi et al., 2009, Rawlins et al., 2009, Murray et al., 1997a) and the ability to control for confounding variables (Cook et al., 2005, Cook et al., 2008, Rawlins et al., 2009, Koles et al., 2005, Murray et al., 1997b) are put forward to support the use of crossover study designs in medical education research.

### **Challenges in using this design and how they will be addressed**

The main challenge associated with the design, conduct, analysis, and interpretation of CRCTs compared with individually randomized trials, is that two different units of measurement—the cluster and the patient—are used (Campbell, 2004). To address this, each will need to be reported carefully.

There are also several challenges raised by the stepped-wedge design. The first group of challenges are statistical. The unidirectional aspect of the crossover in the stepped-wedge design complicates the analysis because the treatment effect can no longer be estimated exclusively from within-cluster comparisons; within-cluster analysis has the potential for bias where the estimated treatment effect may be biased due to failure to model time effects (Hussey and Hughes, 2007). This will be addressed by performing both within-cluster and between-cluster analysis in order to estimate the treatment effect. This approach avoids confounding the treatment effect with changes over time; however, if there are no temporal effects on the outcome then within-cluster analyses can be used to estimate the treatment effect. In addition, time effects will be included in the model for analysis as suggested in the literature (Hughes, 2007, Hussey and Hughes, 2007, Brown et al., 2008).

Another challenge is the possibility that the full effect of the intervention may not be realized until several time intervals following implementation, for example, the intervention being 50% effective after the first time interval, 75% effective after the second time interval and 100% effective after the third time interval (Hussey and Hughes, 2007). Delayed effects from the intensive mentoring for clinical reasoning facilitation are possible, with physiotherapists requiring time to consolidate and make practice changes. The overall effect of these delayed effects would be to reduce power. Such delays can be modelled into the power calculations, and power can be recovered in part by adding additional measurement periods to the end of the trial. However, it is preferable to address this issue by making the time intervals sufficiently long to see the effects of the intervention realized in a single interval (Hughes, 2007, Hussey and Hughes, 2007). To address this, the clinicians who will act as clinical mentors in this study were asked to reflect on their own experience following mentoring programmes from their Masters courses, and estimate what time period they thought would be sufficient to consolidate knowledge and change practice. All responses estimated between 6-12 months. To this end, each time period will be 12 months long, with the intervention delivered at the beginning of the time period and the data collection at the end of the period to allow for the full effects of the intervention to make an impact.

One group of authors (Brown et al., 2008) highlight the amount of data collection required as the main disadvantage of the stepped wedge design, which could make the cost of using the design prohibitive, unless

the study can use routine, or other easily collected data. This study aims to collect patient outcome data at first and final appointments which is part of routine practice in the physiotherapy service at the Cardiff and Vale University Health Board. An additional collection of these outcomes will take place 12 months post discharge by telephone. Demographic and cost-effectiveness data will be collected at the same time in a single compiled questionnaire. This would certainly fit the description of routine, easily collected data.

## **Variables**

For sake of clarity in the methodological design of this study, the variables require explicit definition. The independent variable will be defined as facilitation in clinical reasoning via a clinical mentoring programme. The dependent variables will be defined as patient outcomes and therapist performance. The control variables will be defined as and usual therapist training, patient age, patient condition, patient prognostic barriers, therapist participation, and organizational context.

## **Validity approaches in quantitative methods: Identification of threats to validity and responses**

Creswell (2009) identifies common threats to both internal and external validity. Of particular relevance to this study, internal threats could be due to history, selection, compensatory processes, testing or instrumentation. History threats can be due to external events that can occur during the time that elapses in an experiment, which have an impact on the outcome besides the experimental treatment. To counter this, the research design uses participants from a single profession (physiotherapy), working in a similar environment (musculo-skeletal outpatient departments) in the same NHS health board (Cardiff and Vale); this means that professionally and organizationally the participants should experience the same external events. Selection threats can be due to participants being selected who have certain attributes that predispose them to have better outcomes (e.g., he or she is already more advanced in clinical reasoning, or is brighter or more likely to respond to this form of educational intervention), thus increasing the risk of bias as highlighted by the Cochrane risk of bias tool (Armijo-Olivo et al., 2010, Lundh and Gotzsche, 2008). To counter this, the study has utilised a stepped wedge design (using a one way crossover), so that each participant acts as his / her own control. This does raise the interesting question of different participants' learning styles having a hidden but profound effect on learning effectiveness, and this will be explored using a learning styles questionnaire (Honey and Mumford, 2000a, Honey and Mumford, 2000b). Compensatory threats occur when benefits provided in the experimental group leave participants in the control group resentful, demoralized or feeling devalued, skewing results. Again, the stepped wedge design of this trial counters this threat, with each participant acting as their own control, meaning benefits are provided to both groups, and the fact that during the control phase of this process usual training is being received. Testing threats occur when participants become familiar with the outcome measure being used and remember their responses for later testing. This is countered by the primary outcome measures being *patient* completed outcome measures, and the long-term follow up meaning that recall of previous responses is highly improbable. Instrument threats occur with changes in outcome measures between a pre-test and post-test; in this case, a broad range of outcomes are used to make any desire for changes in outcome measures unnecessary.

External threats to validity in this study could occur from the narrow characteristics of participants in the experiment, care must be taken not to generalize to individuals who do not have the characteristics of participants. Therefore, while methods and results may be of interest to - and have relevance for - other allied health professions, additional experiments would need to be performed to ascertain whether similar results are elicited. Likewise, due to the narrow characteristics of the setting of participants in this

experiment (musculo-skeletal outpatients), care must be taken not to generalize to individuals in other settings (inpatient settings) without further experimentation.

Other threats to validity could involve statistical conclusion threats which occur from inadequate statistical power or violation of statistical assumptions leading the researcher to draw inaccurate inferences or conclusions from the data. In addition, construct validity can be threatened when the researcher uses inadequate definitions and measures of variables. The measures of variables have already been outlined as appropriate, for the variables that have been accurately defined, and the research study has been appropriately powered.

